# Effects of perioperative transcutaneous electrical acupoint stimulation on monocytic HLA-DR expression in patients undergoing coronary artery bypass grafting with cardiopulmonary bypass: study protocol for a double-blind randomized controlled trial

**DOI:** 10.1186/s13063-019-3889-z

**Published:** 2019-12-30

**Keywords:** CABG, TEAS, Immunosuppression, mHLA-DR

## Abstract

**Background:**

Cardiac surgery involving cardiopulmonary bypass (CPB) is known to be associated with a transient postoperative immunosuppression. When severe and persistent, this immune dysfunction predisposes patients to infectious complications, which contributes to a prolonged stay in the intensive care unit (ICU), and even mortality. Effective prevention and treatment methods are still lacking. Recent studies revealed that acupuncture-related techniques, such as electroacupuncture and transcutaneous electrical acupoint stimulation (TEAS), are able to produce effective cardioprotection and immunomodulation in adult and pediatric patients undergoing cardiac surgery with CPB, which leads to enhanced recovery. However, whether perioperative application of TEAS, a non-invasive technique, is able to improve immunosuppression of the patients with post-cardiosurgical conditions is unknown. Thus, as a preliminary study, the main objective is to evaluate the effects of TEAS on the postoperative expression of monocytic human leukocyte antigen (-D related) (mHLA-DR), a standardized “global” biomarker of injury or sepsis-associated immunosuppression, in patients receiving on-pump coronary artery bypass grafting (CABG).

**Methods:**

This study is a single-center clinical trial. The 88 patients scheduled to receive CABG under CPB will be randomized into two groups: the group receiving TEAS, and the group receiving transcutaneous acupoint pseudo-electric stimulation (Sham TEAS). Expression of mHLA-DR serves as a primary endpoint, and other laboratory parameters (e.g., interleukin [IL]-6, IL-10) and clinical outcomes (e.g., postoperative infectious complications, ICU stay time, and mortality) as the secondary endpoints. In addition, immune indicators, such as high mobility group box 1 protein and regulatory T cells will also be measured.

**Discussion:**

The current study is a preliminary monocentric clinical trial with a non-clinical primary endpoint, expression of mHLA-DR, aiming at determining whether perioperative application of TEAS has a potential to reverse CABG-associated immunosuppression. Although the immediate clinical impact of this study is limited, its results would inform further large-sample clinical trials using relevant patient-centered clinical outcomes as primary endpoints.

**Trial registration:**

ClinicalTrials.gov, NCT02933996. Registered on 13 October 2016.

## Background

Cardiac surgery involving cardiopulmonary bypass (CPB) is known to be associated with immune dysfunctions characterized by initial pro-inflammatory response and subsequent anti-inflammatory response [1]. If the following anti-inflammatory response is persistent and severe, it will lead to a long-lasting immunosuppressive state. This may result in an increased susceptibility to postoperative infectious complications, such as pneumonia or impaired wound healing, and thus a prolonged stay in the intensive care unit (ICU), or even mortality [2–5].

During CPB surgery, the exposure of blood to the non-physiological surfaces of the CPB apparatus [6], cardiac arrest and ischemia/reperfusion injury of organs [7], and translocation of endotoxins (lipopolysaccharide, LPS) across the ischemic gut wall [8–10] trigger a pronounced pro-inflammatory response, which is characterized by circulating cytokines, activation of endothelial cells and neutrophils, complement activation, circulating arachidonic acid metabolites, platelet-activating factors, and endothelins [11, 12]. As a physiologic countermeasure to ameliorate this harmful overactivation of innate immunity, a compensatory anti-inflammatory response often follows, which is known to cause a transient immunosuppression. It comprises secretion of anti-inflammatory cytokines such as interleukin (IL)-10 by monocytes and T cells, down-regulation of inflammatory cell surface receptors on neutrophils, impaired monocytic response to bacterial endotoxins [13, 14], reduced production of interferon-γ (IFNγ), IL-2, and tumor necrosis factor (TNF)-α, as well as peripheral blood mononuclear cell (PBMC) proliferation in response to stimulation with phytohemagglutinin [15]. Generally, this immunosuppression is temporary and can be restored to normal. However, when serious and persistent, this immune imbalance is considered to contribute to postoperative infectious complications. Unfortunately, the counterbalancing long-lasting immunosuppressive responses still remain a clinical challenge.

Acupuncture is an ancient, non-drug treatment technology originating in China, which has been widely used worldwide. Recently, more and more studies have revealed that acupuncture is able to effectively regulate the function of the immune system, and this technique has been clinically regarded as a primary or adjuvant therapy measure for some immune-related diseases (e.g., asthma, allergic rhinitis, and rheumatic arthritis) [16–18]. In recent years, acupuncture-related techniques began to be applied to cardiac surgery for better recovery. Yang et al. [19] have shown that for adult patients undergoing heart valve replacements, electroacupuncture (EA) pretreatment can alleviate cardiac ischemia-reperfusion injury indicated by reduced overall serum troponin I release and dosage of inotropic drug use after surgery. Also, the ICU stay time can be shortened. Subsequently, pretreatment of transcutaneous electric acupoint stimulation (TEAS), a non-invasive acupoint stimulation technique, has produced similar cardioprotective effects in pediatric patients undergoing cardiac surgery. Moreover, alleviated inflammation indicated by reduced C-reactive protein (CRP) level in the early postoperative period was observed [20].

Experimental studies also demonstrate that EA at the Zusanli (ST36) acupoint suppresses surgical trauma stress-induced lymphocyte apoptosis [21] and increases lymphocyte proliferation and IL-2 production in surgically traumatized rats [22–24] and IFNγ production of the spleen in mice [25]. Wang et al. further indicated that EA administration after surgical trauma increased Th1 cytokine protein and mRNA expression (IL-2 and IFNγ), and suppressed Th2 cytokine protein and mRNA expression (IL-4 and IL-10), involving the signaling pathways of ERK1/2, p38, NF-κB, and AP-1 in rats. These findings suggest that EA may improve immune suppression after surgical trauma [26].

TEAS involves no risk of infection, needle-induced contagious disease, or fear of stimulation and is more “user friendly” with minimal training, which is more convenient for clinical application [27]. However, whether perioperative application of TEAS is able to improve postoperative immunosuppression of patients receiving on-pump CABG is unknown.

In the current study, we will attempt to evaluate potential TEAS-induced reversal of CABG-associated immunosuppression. Previous clinical studies have shown that whether the patient is in a conscious state (i.e., preoperative or postoperative) or an anesthetic state, TEAS or EA applied to various surgical operations can produce beneficial effects, such as preventing hyperglycemia [28], reducing intraoperative opioid consumption [29], relieving post-hemorrhoidectomy-associated pain [30], and improving immune and stress responses to surgery [31]. In order to maximize the possible benefit of TEAS, the perioperative administration (i.e., preoperative, intraoperative, and postoperative) of TEAS will be chosen in our trial.

Considering that this is a preliminary monocentric study, monocytic human leukocyte antigen (-D related) (mHLA-DR), a standardized “global” biomarker of injury- or sepsis-associated immunosuppression, serves as a primary endpoint, and other laboratory parameters (e.g., IL-6, IL-10) and clinical outcomes (e.g., postoperative infectious complications, ICU stay time, and mortality) as the secondary endpoints. Monocytic HLA-DR is a major histocompatibility complex (MHC) class II molecule and is predominantly expressed on monocytes/macrophages [32]. Its surface expression is indispensable for antigen presentation [32]. Increased mHLA-DR expression reflects activation of immune cells, while diminished expression exhibits a phenotype with down-regulation of antigen-presenting capacity and a shift from pro- to anti-inflammatory cytokine production [33, 34]. Moreover, surface expression of mHLA-DR is crucial for induction of adaptive immune responses [32, 35]. More importantly, accumulated clinical evidence has indicated that its persisting decreased expression is associated with adverse clinical outcomes (e.g., secondary infection risk, mortality) in patients with trauma [36], burns [37], pancreatitis, [38, 39] solid organ transplantation [40], hepatic [41] or renal injury [42], stroke [43], myocardial infarction/heart failure and cardiac arrest [44–47], as well as sepsis [48]. The same is true of cardiac surgery with CPB. The quantification of mHLA-DR expression shows the best predictive power on outcome in pediatric and adult patients. Postoperative reduced mHLA-DR was associated with increased length of ICU stay/mechanical ventilation and development of postoperative sepsis [49, 50].

In addition, some immune indicators, such as high mobility group box 1 protein (HMGB1) and regulatory T cells (Treg), possibly related to the mechanism of TEAS would also be measured. HMGB1, originally described as a DNA-binding protein and passively released by necrotic cells and actively released by macrophages/monocytes, was discovered to be an essential cytokine that mediates the response to infection, injury, and inflammation [51]. Our previous animal study has shown that EA can inhibit excessive release of HMGB1 following myocardial ischemia and attenuate the associated inflammatory responses and myocardial injury during reperfusion [52]. Recently, HMGB1 was found to directly enhance the immune inhibitory functions of Treg and limit the number and activity of conventional T cells [53, 54].

Treg cells are responsible for limiting tissue damage and inflammation associated with both innate and adaptive immune responses [55]. However, overactivation of Treg contributes to immunosuppression [56]. It was shown that the population of Treg in PBMCs was significantly increased at 48 h and 96 h after CABG with CPB [57], which may contribute to CABG-associated immunosuppression. Thus, we speculate that the potential inhibition of excessive HMGB1 release of TEAS, consequently leading to attenuated function of Treg, may be associated with TEAS-induced reversal of immunosuppression, characterized by increased mHLA-DR.

### Objective

The primary objective of the study is to evaluate the effects of perioperative TEAS on mHLA-DR expression in patients undergoing CABG with CPB.

## Methods/design

### Study design

This study is a preliminary, single-center, double-blind, randomized and controlled clinical trial (number of samples, *n* = 88) to explore the effects of TEAS therapy on improvement of postoperative immunosuppression indicated by diminished HLA-DR expression of patients receiving CABG (Fig. 1). The trial will commence after ethical approval has been obtained from the Ethics Committee of Shuguang Hospital Affiliated to Shanghai University of Traditional Chinese Medicine. All study-related procedures will be performed only after subjects have given their written informed consent. The trial is designed following the Consolidated Standards of Reporting Trials (CONSORT) guidelines, the Standard Protocol Items: Recommendations for Interventional Trials (SPIRIT) checklist (Additional file 1), and Standards for Reporting Interventions in Controlled Trials of Acupuncture (STRICTA) recommendations.

**Fig. 1 Fig1:**
[figure not shown]
Flowchart of the study

### Participants

#### Current sample size justification

We calculated the sample size from the pilot study in our hospital based on the primary outcome: monocytic human leukocyte antigen DR (mHLA-DR). In that study, the expression of mHLA-DR 3 days after surgery was 36.17 ± 5.42% in the TEAS group and 27.33 ± 3.50% in the Sham TEAS group, with a power of 80% and a 5% type I error rate. Assuming that the dropout rate is 10%, 88 patients (*n* = 44 for each group) are needed.

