### Statistical analysis

All statistical analyses of the data will be performed using SPSS program V.21.0 (SPSS Inc., Chicago, IL, USA). A *P* value < 0.05 will be considered statistically significant. The intention-to-treat (ITT) approach will be used. Measured data will be expressed as mean ± SD (^−^*x*± *s*) if it obeys a normal distribution or an approximate normal distribution. The median (interquartile range [IQR]) will be used if the data do not obey the normal distribution and count data will be expressed in terms of the number of cases.

To analyze the primary outcome, the expression of mHLA-DR (the percentage of HLA-DR+/CD14+ cells in all CD14+ cells) will be calculated by repeated measures analysis of variance (ANOVA), and the comparisons between the two groups will be made using the Student’s *t* test. For the secondary outcomes, we will use chi-square tests for categorical data and repeated measures ANOVA or the Wilcoxon rank sum test for continuous data, according to whether the data are normally distributed. The variance analysis will be performed for the difference between the two groups and within a group. A stratified analysis will be performed to control the confounding factor if necessary. Data analysis will be conducted by statisticians who are independent of the research team.

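### The 88 patients said to be needed do not follow from the printed pilot figures, which at 80% power call for about 14

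*Protocol article*

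**What the plan says.** The section on current sample size justification bases the calculation on a pilot study at the same hospital and on the primary outcome. For the active arm it reports that "the expression of mHLA-DR 3 days after surgery was 36.17 ± 5.42% in the TEAS group". The sham arm's figure is printed as 27.33 ± 3.50%. The design targets are 80% power and 5% type I error. The conclusion reads "Assuming that the dropout rate is 10%, 88 patients" and puts the requirement at 44 per group.

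The section does not say whether the ± figures are SDs or standard errors. It also omits the number of pilot patients, whether the 5% is one- or two-sided, and the per-group number before dropout. The Statistical analysis section sets the article's reporting convention for normally distributed data, "Measured data will be expressed as mean ± SD", and names Student's t test for the between-group comparison of mHLA-DR. Allocation is 1:1. The article gives no other target effect, no multiplicity allowance and no safety margin.

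**The concern.** The paragraph reads as a complete derivation, with two means, two measures of spread, power, type I error, dropout and a result. A difference of 8.84 points against spreads of 3.5 to 5.4 is very large, and a comparison of that kind needs only a handful of patients per group. A requirement of 44 per group is out of line with it.

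What is at stake is the meaning of the trial's size. If the spread really is about 4.6 points, 88 patients give 80% power for a difference about one third of the pilot's. If 88 was meant to give 80% power for the full pilot difference, the planning SD must have been about three times the printed one. These are different designs, and the text does not say which one was intended. The Discussion says the results will inform larger trials, so a power statement that cannot be reproduced could mislead their planning and the reading of this result.

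**Working it through.** **Inputs** (sample size section unless noted)
- Means 36.17 and 27.33, so the difference is 36.17 − 27.33 = 8.84 points.
- Spreads 5.42 and 3.50, read as SDs under the convention in Statistical analysis.
- Power 80%, type I error 5%, dropout 10%.
- Allocation 1:1 (Randomization and blinding).
- Student's t test (Statistical analysis).
- Two-sided testing is my assumption; one-sided is shown as a variant.

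**Standardised difference**
- Pooled SD = √[(5.42² + 3.50²)/2] = √[(29.38 + 12.25)/2] = 4.56.
- d = 8.84 / 4.56 = 1.94.

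**Attempt to reproduce 88**
- Normal approximation: n per group = 2 × (1.96 + 0.84)² / 1.94² = 15.7 / 3.75 = 4.2, so 5. Then 5/0.9 = 5.6, so 6 per group and 12 in total.
- Exact two-sample t test (noncentral t): 5 per group gives 76.5% power and 6 per group gives 85.6%, so 6. Then 6/0.9 = 6.7, so 7 per group and **14 in total**.

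**Variants**

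| Choice | Evaluable per group | Total after dropout |
|---|---|---|
| One-sided 5%, normal approximation | 4 | 10 |
| One-sided 5%, t test | 5 | 12 |
| Two-sided 5%, t test (main case) | 6 | 14 |
| Two-sided, larger SD (5.42) in both groups, t test | 8 | 18 |
| Two-sided, power 90%, t test | 7 | 16 |
| Two-sided, power 95%, t test | 9 | 20 |
| Two-sided, power 99%, t test | 11 | 26 |
| Alpha 0.05/3, power 80%, t test | 8 | 18 |
| SDs added together (8.92, not a valid choice), two-sided, normal approximation | 16 | 36 |

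Standard choices at the stated 80% power and 5% error run from about 10 to 18. Higher power, a stricter alpha and even adding the SDs together do not come near 88.

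**What 88 delivers**
- Evaluable patients: 88 × 0.9 = 79.2, about 79, or 39 to 40 per group.
- Power for 8.84 points with SD 4.56 is above 99.99% at either 39 or 40 per group.
- Difference detectable with 80% power, two-sided 5%: 0.64 SD at 39 per group and 0.63 SD at 40. With SD 4.56 that is 2.93 and 2.89 points, about one third of 8.84 (8.84/3 = 2.95).
- SD at which 8.84 points would have exactly 80% power: 13.8 at 39 per group and 13.9 at 40. That is about three times the printed 4.56 (13.8/4.56 = 3.0).

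**The case against.** **The ± figures may be standard errors.** The paragraph does not label them, and the convention in Statistical analysis describes the trial's data, not the pilot's. If they were SEs from 9 patients per group, the SD would be 4.56 × √9 = 13.7, the t test would need 39 per group, and 39/0.9 = 43.3 rounds up to 44. A reader might infer that this is what happened, but the documents do not support it. The pilot size is not given and has to be picked to fit: 8 per group would give 39 after dropout and 10 would give 48. The only convention the article states is SD. The SE reading is a fair question for the sponsor and no more. If it were true, the paragraph would still need correcting.

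**88 may have been chosen generously.** A larger trial than the minimum is legitimate, and on the printed inputs 88 more than meets an 80% target. But the paragraph says the number was calculated from the pilot on the primary outcome and is needed. It states no margin and no other purpose.

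**An article condenses the full protocol.** That would excuse missing detail. Here the main inputs and the result are printed, and they disagree.

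**The consequence is limited.** This stands in part. The study is described as preliminary with a biomarker endpoint. This version is dated October 31, 2019, with recruitment due to end on December 31, 2019, so no enrolment decision is likely to turn on the correction. It remains a wrong statement about the basis of the primary comparison.

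**Conclusion.** The stated size does not follow from the stated inputs. Read as SDs, the pilot figures require about 14 patients in total (roughly 10 to 18 across standard choices), so 88 is about six times the number they support (88/14 = 6.3). Power at about 40 evaluable per group is above 99.99%, not 80%. This rests on ± meaning SD and, for the figure of 14, on a two-sided t test; the conclusion is the same for a one-sided test.

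Two stronger readings are not supported. A reader might infer that the trial is underpowered. On the printed inputs it is not; power for 8.84 points would fall below 80% only if the true SD exceeded about 13.8 to 13.9, and nothing in the article shows that. A reader might also infer that dropout was handled wrongly, as 40 × 1.1 = 44 instead of 40/0.9, which rounds up to 45. No pre-dropout number or formula is printed, and 39/0.9 rounds up to 44, so no inflation error is shown.

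**What to change.** Keep 88 and rewrite the sample size paragraph.
1. State whether the ± figures are SDs or standard errors, and give the number of pilot patients per group.
2. If 88 came from other inputs, print the effect, SD and sidedness that yield it.
3. Otherwise, state what 88 delivers. For example: with about 79 evaluable patients the trial has 80% power, at two-sided 5%, to detect a difference of about 0.64 SD in Day 3 mHLA-DR. Add the equivalent of about 2.9 points only once the SD is confirmed as 4.56. If 8.84 points is the intended target, say that this implies an SD near 13.8 to 13.9 and justify it.
4. Remove the claim that the printed pilot figures require 88 patients at 80% power.

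The cost is one paragraph of text and a check of the pilot records. The number of patients, the procedures and the analysis do not change.

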#### Subject recruitment

Patients will be recruited from the Department of Thoracic and Cardiovascular Surgery, at Shuguang Hospital Affiliated to Shanghai University of Traditional Chinese Medicine. Potentially eligible subjects who are scheduled for CABG under CPB for coronary disease will be invited to participate. Patients will be referred from a cardiothoracic surgeon, and then a research assistant will approach the subjects in the general ward pre operation. Patients will then be screened and consented for the study. Following the consent, eligible participants will be block randomized into two groups: (1) TEAS group (*n* = 44) and (2) Sham TEAS group (*n* = 44). All patients will receive standard operative procedure and postoperative analgesia management. The patients of the TEAS group will receive TEAS therapy in the perioperative period, and the Sham TEAS group will receive “pseudotherapy” performed without electrical stimulation in the perioperative period. Assessments will be conducted during the perioperative period until 30 days after surgery.

#### Inclusion criteria

The inclusion criteria are as follows:
Aged 18–75 years, male and femalePatients diagnosed with coronary disease and scheduled to receive CABGBody mass index (BMI) measure of 18.5 kg/m^2^ < BMI ≤ 30 kg/m^2^Patients with Grade of I–III according to American Society of Anesthesiologists (ASA)Patients first receiving CABG under extracorporeal circulation.

#### Exclusion criteria

The exclusion criteria are as follows:
Presence of surgical incision or scar at Zusanli acupoint (ST36)/Shenshu (BL23) acupointPatients with local skin infection at acupointPatients with nerve injury on upper or lower limbsPatients with history of spinal surgeryPatients who have participated in another clinical trial in the last 4 weeksPatients using a pacemakerPatients who have pain before surgery who are using a central analgesic drug or those who are drug abusers (e.g., opioids) or dependent usersPatients who have severe central nervous system disease or severe mental diseasePatients with an alcoholic historyPatients who have received emergency coronary bypass operation due to acute myocardial infarction.

### Randomization and blinding

A computer generates a random number sequence. The allocations will be printed and placed in separate sealed envelopes. The patients will be randomly divided into either the TEAS group or the Sham TEAS group in a 1:1 ratio. We set a blind code in case patients have adverse effects. The random code and blind code will be conducted using opaque envelopes by a “third party” independent of the study. The envelopes will be sealed and shuffled, and the assignment records will not be disclosed until the end of the study. Trial participants, cardiothoracic surgeons, anesthesiologists, outcome assessors, and data analysts will be blinded to the treatment allocation to minimize potential sources of bias. Only the nurse of the anesthesiology department (having received specialized acupuncture training) will know the participants’ group allocations. However, this nurse will not know any other information about the patients.

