### Interventions

This trial will include two groups: the TEAS group and the group receiving transcutaneous acupoint pseudoelectric stimulation (Sham TEAS). In each group, there will be 44 patients receiving CABG with CPB. The patients of the TEAS group will receive TEAS therapy in the perioperative period, and in the Sham TEAS group, pseudotherapy without actual electrical stimulation will be performed in the perioperative period. The intervention details are as follows:
Selection of acupoints: Zusanli acupoint (ST36), Shenshu acupoint (BL23) (see Figs. 2 and 3):
Zusanli location: outside of the shank, 3 cun (10 cm) below Dubi acupoint (ST35) and a finger’s width (middle finger) to tibial front edgeShenshu location: below the spinous process of the second lumbar vertebra, 1.5 cun (5 cm) to the central lineStimulation timing: before anesthesia plus intraoperative plus postoperative (see Fig. 4):
30 min before anesthesia: one stimulation for 30 minIntraoperative: stimulation for the whole coursePostoperative: 0–24 h: four times of stimulation (30 min per stimulation). 5–6 h after the surgery (the first time), 11–12 h after the surgery (the second time), 17–18 h after the surgery (the third time), 23–24 h after the surgery (the fourth time)TEAS parameters
Frequency: 2/100 Hz alternatingIntensity: 15 mALow-frequency electronic pulse therapeutic device G6805-2 (Huayi, Shanghai, China) (see Fig. 5)Current intensity: main difference between the study group and control group
TEAS group: the acupoints, including Zusanli and Shenshu, are identified before electrical stimulation with surface electrodes (Fig. 6). Selection of these acupoints was based on a consensus between the acupuncturists of the study.Sham TEAS group: No electrical stimulation is actually performed in the Sham TEAS group. In the Sham TEAS group, pseudostimulation is provided by deliberately connecting the electrodes to the incorrect output socket of the EA device; thus, there is no flow of electric current. Patients can see the output light flashing, but no current is transmitted throughout the procedure. Patients would be told that the stimulation frequency selected was not perceivable by humans.Anesthesia protocol
Medication before the anesthesia: morphine 0.1 mg/kgAnesthesia induction

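### Block randomisation is stated, but so is shuffling of the sealed envelopes; as written, the blocking is not achieved and the order of the computer sequence is lost

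*Protocol article*

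**What the plan says.** Two sections of the protocol article describe the allocation.

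- **Subject recruitment:** after consent, "eligible participants will be block randomized into two groups", 44 to TEAS and 44 to Sham TEAS. No block size is given.
- **Randomization and blinding:** "A computer generates a random number sequence. The allocations will be printed and placed in separate sealed envelopes". The ratio is 1:1, and an independent third party handles the codes in opaque envelopes. Then "The envelopes will be sealed and shuffled", and "the assignment records will not be disclosed until the end of the study".

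Randomization and blinding does not mention blocks. It does not say that envelopes carry sequence numbers, that they are opened in a set order, or that shuffling is limited to envelopes of the same block.

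**The concern.** A permuted block is a property of order: within each consecutive run of a fixed length, the two arms appear equally often. The computer list has that property only while its order is kept, and shuffling the sealed envelopes replaces that order with a new one made by hand. The article therefore states a method and then a step that undoes it. This is a conflict between two stated steps, so it differs from a detail that a journal article leaves to the full protocol.

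Two things are at stake. The first is balance over calendar time. Trial status gives recruitment from 1 December 2017 to 31 December 2019, and the primary outcome is a flow-cytometry percentage, so blocking would have kept the arms level if the assay or care changed over that period. The second is traceability. With an ordered list one can check that the k-th patient received the k-th allocation. After a shuffle there is no generated order to check against. The article also says that it follows CONSORT and SPIRIT, so the method of sequence generation will be reported, and calling it blocked would misdescribe what was done.

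**Working it through.** **1. The two statements side by side.** Blocking requires use in generated order, and shuffling discards that order. Two unstated arrangements would reconcile them: shuffling only within each balanced block, or restoring list order after the shuffle by means of envelope numbers. Neither appears in the article.

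**2. Inputs for the size of the effect.**
- 44 envelopes per arm, 88 in all, from Interventions: "In each group, there will be 44 patients receiving CABG with CPB".
- Assumption: all 88 were shuffled together, once and fairly.
- Assumption: block sizes of 4 and 6, for comparison only, because the article gives none.

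The plan states no figure of its own for imbalance, so there is none to reproduce.

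**3. Imbalance at the halfway point.** After n patients, the number X on TEAS is hypergeometric:

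P(X = k) = C(44, k) × C(44, n − k) / C(88, n), with arm difference D = |2k − n|.

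For n = 44:

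| D | 0 | 2 | 4 | 6 | 8 or more |
|---|---|---|---|---|---|
| Probability | 0.169 | 0.309 | 0.236 | 0.151 | 0.135 |

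- P(D ≥ 6) = 0.151 + 0.135 = 0.286
- P(D ≥ 8) = 0.135

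For n = 22 or n = 66, P(D ≥ 6) = 0.218.

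**4. The same point with intact blocks.** Blocks of 4: 44 = 11 × 4, so D = 0. Blocks of 6: 44 = 7 × 6 + 2, so only two patients lie in an open block and D is at most 2.

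**5. Whether blocks could survive by chance.** After a full shuffle, a given run of 4 is split 2:2 with probability C(44, 2)² / C(88, 4) = 0.38. All 22 such runs are balanced with probability 6²² / C(88, 44), about 5 × 10⁻⁹.

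**6. Largest imbalance at any time.** In 20,000 simulated shuffles of 44 + 44 envelopes, the largest running difference had median 7 and 95th percentile 12, and it exceeded 4 in 94% of shuffles. With intact blocks of 4 it cannot exceed 2.

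**7. Final balance.** If all 88 envelopes are used, the split is 44:44 whatever the order.

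**The case against.** The strongest reply is that the calculation assumes one shuffle across all 88 envelopes, which the article does not say. Shuffling a balanced set within each block fits both sentences. This stands, and it is why the figures are conditional. It does not remove the conflict, because the article mentions no such limit.

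A second reply is that little harm follows. This also stands in part. A fair shuffle does not bias the comparison, the final split is exact if all envelopes are used, and the article describes no interim analysis. Even a 25:19 split at 44 patients keeps 4 × 25 × 19 / 44² = 98% of the precision of an even split in that half, and 26:18 keeps 97%. Drift in the assay or in care is a possibility, not something the article reports, and Quality control fixes the main staff at this single centre.

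A reader might infer more: that the audit trail is destroyed, that a skipped or re-drawn envelope could never be detected, or that concealment is weakened. The article does not support this. It is silent on envelope numbers and logs, which an article may leave to the full protocol, and silence does not show that they were absent. It does state sealed opaque envelopes, an independent third party and retained assignment records, so the arm each patient received may well be documented. Shuffling sealed opaque envelopes does not in itself reveal the next allocation. What the shuffle removes is narrower: the check of assignments against the generated order.

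**Conclusion.** The point holds as an inconsistency between two stated steps. Unless the shuffle was confined to blocks or the envelopes were then used in list order, the allocation is an unblocked random permutation and should not be called blocked.

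On the assumption of one shuffle of 44 + 44 envelopes, the cost is balance over time: a chance of 0.29 that the arms differ by 6 or more at the midpoint and 0.14 that they differ by 8 or more, where assumed intact blocks would give 0 (size 4) or at most 2 (size 6). The ability to verify assignments against the sequence order is lost as well. The validity of the treatment comparison and the final 1:1 ratio are not affected. The point is worth correcting, but it does not threaten the trial's result.

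**What to change.** In Randomization and blinding, delete the shuffling step. State that the third party numbers the opaque envelopes in the computer-generated block order, and that they are opened in that order and logged against the patient code.

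Recruitment was due to end on 31 December 2019, one day after the article's publication date, so most envelopes will already have been used. For any that were shuffled, remove the term block randomized from Subject recruitment, describe the allocation as unblocked, and reconcile the assignment records with the computer list as far as possible. If the shuffle was in fact within blocks, or list order was restored, say so and give the block size.

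For future envelopes the cost is a sentence and a log. For those already used it is a corrected description and a reconciliation of 88 records at most. The sample size does not change.
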